### Procedure

A Norwegian website (www.bodyproject.no) has been designed to facilitate recruitment and project profiles are posted on Facebook and Instagram. The link will be shared via our online platforms, including Facebook, Instagram, and TikTok. Also, advertisement campaigns on social media will be run nationally. Individuals express interest by sending an e-mail to a *Body Project* mailbox hosted by Oslo University Hospital, which leads to a screening phone call to determine eligibility based on the inclusion criteria described above. In this screening call eligible participants verbally confirm to experience at least some body dissatisfaction. After providing informed consent, participants will complete baseline assessment (pretest) before being randomized into one of three arms: (i) peer-led virtual *Body Project* groups; (ii) clinician-led virtual *Body Project* groups; and (iii) educational video control group. Assessment will be repeated post intervention (posttest) and follow-up assessment after 6-months, 1-year, and 2-years. ED diagnostic interviews are conducted at baseline, 1-year, and 2-year assessments by research staff who are masked to the condition to which each participant will be randomized. Online assessment will be conducted via an online survey (Viedoc) hosted by Clinical Trials Unit (CTU), Oslo University Hospital. Randomization will be conducted by Viedoc once baseline assessment is completed. Virtually delivered *Body Project* group sessions will be implemented by use of Microsoft Teams, administered by Oslo University Hospital. Adaptations required for virtual script delivery include administration of home exercises via e-mail and using the chat function for summarizing themes during in-session group discussions rather than white boards or flip-charts used for in-person *Body Project* groups. This study is funded by the Norwegian Health Authority Region South-East (reference 2,023,032).

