### Assessment

All measures are translated to Norwegian. Only the Eating Disorder Examination Questionnaire (EDE-Q) and Eating Disorder Assessment for DSM-5 (EDA-5) are validated in Norwegian, while the psychometric properties of the remaining measures are validated in English. See details below:

*Thin-ideal internalization*: the 8-item Ideal-Body Stereotype Scale-Revised (IBSS-R) [36] to assess endorsement of thin-ideal using a Likert scale ranging from 1 = strongly disagree to 5 = strongly agree. It has shown internal consistency (α = 0.91), 2-week test-retest reliability (*r* = .80), predictive validity for future ED onset, and sensitivity to detecting intervention effects [33].

*Body dissatisfaction*: ten items from the Body Parts Scale [37] to assess dissatisfaction with body parts with a Likert scale ranging from 1 = extremely dissatisfied to 6 = extremely satisfied. It has shown internal consistency (α = 0.94), 3-week test-retest reliability (*r* = .90), predictive validity for future ED onset, and sensitivity to detecting intervention effects [33].

*Negative affect*: 20 negative items from the Positive and Negative Affect Schedule – Revised (PANAS-X) [38] to measure negative affect. It has high internal consistency (mean Cronbach’s α of 0.94), test-retest reliability (r = .78), and convergent validity [15].

*ED symptoms*: The Eating Disorder Examination Questionnaire (EDE-Q) [39] is a self-report 28-item questionnaire of specific eating disorder psychopathology based on the Eating Disorder Examination (EDE) diagnostic interview [40]. Reponses range from 0 to 6 with higher scores indicating higher levels of ED psychopathology. The EDE-Q consists of the four subscales *eating restraint*, *eating concern*, *shape concern*, and *weight concern* and is previously translated and validated in Norwegian men and women [41, 42].

*Appearance ideal internalization and pressures*: the Social Attitudes Towards Appearance Questionnaire 4 – Revised (SATAQ-4R) for women [43] consists of 31 items with subscales which measure: internalization thin/low body fat, internalization of muscularity, internalization of general attractiveness, pressures from family, pressures from peers, pressures from significant others, and pressures from media. Internal consistency (Cronbach’s α ≥ 0.82) and construct validity have been demonstrated.

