### Statistical analyses

*Model building.* Intent-to-treat (ITT) analyses of condition effects will be evaluated using mixed effects growth models fit with SAS 9.2 PROC MIXED [50]. Individual variability in outcomes from posttest to 2-year follow-up was modeled adjusting for pretest outcome values. Following Singer and Willet [51], when constructing the longitudinal models we will (a) examine empirical growth plots; (b) fit an unconditional means model; (c) fit an unconditional linear growth model; (d) fit unconditional non-linear models; and (e) compare models of longitudinal change using the Akaike Information Criterion. Condition, time (coded in months since posttest), and a condition × time interaction will be added to the unconditional model. We will estimate a growth model for each continuous outcome. We will report the results of planned contrasts from these models, contrasting each pair of conditions, reporting condition differences in the model implied least-square means derived from the time and condition × time interactions at 1- and 2-year follow-up. We will report effect sizes that are equivalent to Cohen’s *d* [52]. We will use full information maximum likelihood (ML) estimation to impute missing data because this intent-to-treat approach produces more accurate and efficient parameter estimates than alternative analytic approaches such as analyzing only participants who provide complete data, making multiple imputation the recommended procedure for handling missing data [53]. Missing data will be imputed using PROC MI using baseline levels of the outcomes, condition, and demographic factors (age, race, and parent education). Based on the recommendations [53], we will impute 50 data sets. Model parameters and standard errors were combined following Rubin [54] and implemented using PROC MIANALYZE. Cox proportional hazard models, fit with STATA [55] will test whether eating disorder onset over 2-year follow-up was significantly lower in each condition versus each other condition. Schoenfeld residuals will be examined to test the proportional hazards assumption. Hazard ratios and number needed to treat (NNT; [56]) are provided as measures of effect size. Because hazard models accommodate right censoring, we will not impute missing incidence data. Given that 88% of the effects from previous *Body Project* trials have replicated in 22 controlled trials from independent teams [15], we will use a p-value of 0.05 for all inferential tests because this usually balances risk for type I and type II errors.

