
### Power calculation

Sample size calculation was made for incidence of EDs assessed over a 2-year follow up via diagnostic interviews as the primary endpoint. Incidence rates were obtained from the previous Swedish virtual *Body Project* RCT [16]. Based on this trial we postulated a difference in incidence of EDs of 8.8% and 2% between groups, and a hazard ratio of 0.26 during 2 years of follow-up. Then, with a significance level of 5% and a power of 90% the estimated number of patients needed was 147 in each arm, the total number needed was 441.

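### The onset Cox models are described by condition only, and the reason given for ignoring missing onset data leaves out the independent-censoring assumption; one pre-specified baseline severity covariate would relax it at almost no cost.

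*Protocol article*

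**What the plan says.** All references are to the Protocol article.

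- **Endpoint.** Power calculation: "Sample size calculation was made for incidence of EDs assessed over a 2-year follow up via diagnostic interviews as the primary endpoint".
- **Onset model.** Statistical analyses: "Cox proportional hazard models, fit with STATA [55] will test whether eating disorder onset over 2-year follow-up was significantly lower in each condition", each condition being compared with each other one. No covariate is named, and none is excluded.
- **Missing onset data.** Same section: "Because hazard models accommodate right censoring, we will not impute missing incidence data".
- **Continuous outcomes.** Same section: "Individual variability in outcomes from posttest to 2-year follow-up was modeled adjusting for pretest outcome values". Their missing values are handled from baseline information: "Missing data will be imputed using PROC MI using baseline levels of the outcomes, condition, and demographic factors (age, race, and parent education").
- **Baseline severity is available.** Assessment: "The Eating Disorder Examination Questionnaire (EDE-Q) [39] is a self-report 28-item questionnaire of specific eating disorder psychopathology". Procedure: "participants will complete baseline assessment (pretest) before being randomized into one of three arms".
- **Interview times.** Procedure places the diagnostic interviews at baseline, 1 year and 2 years.

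**The concern.** A Cox model copes with right censoring when, given the terms in the model, those who leave have the same onset hazard as those who stay. With condition as the only term, this must hold within each arm across all levels of severity. The article's rationale does not say so. In the same paragraph, the continuous outcomes are allowed dropout that depends on baseline values, because those values enter both the model and the imputation. The endpoint used for sizing therefore rests on the stronger missing-data assumption.

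The article itself regards baseline status as prognostic. Its Assessment section credits the thin-ideal internalization and body dissatisfaction scales with predicting later onset, although it does not say this of the EDE-Q. The arms also ask for different things: live groups with role-play and home exercises, or videos watched alone. If more severe participants left one arm more readily than another, the HR would partly reflect who stayed.

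**Working it through.** **Inputs from the article.** Incidence 8.8% and 2%, HR 0.26, 147 per arm, 5% significance, 90% power.

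**The plan's own figure.** Schoenfeld events for two-sided 5% and 90% power: 4 × (1.96 + 1.2816)² / (ln 0.26)² = 42.03 / 1.815 = 23.2, so 24. At a mean incidence of 5.4% this is 24 / 0.054 = 444 in two arms, or 222 per arm. The stated 147 per arm is not reproduced. That is a separate matter, and this point does not depend on it.

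**Information available.** Expected onsets in one comparison with control: 147 × 0.088 + 147 × 0.02 = 12.9 + 2.9 = 15.9. Standard error of the log HR: √(1/12.9 + 1/2.9) ≈ 0.65. Peer versus clinician: 2 × 147 × 0.02 ≈ 6 onsets. All 147 are taken as at risk. Participants with an eating disorder at baseline may be enrolled, so the real number at risk may be lower.

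**Assumptions, since the article gives no figures.** Severity x is standard normal. The onset HR per SD is e^γ = 1.5, 2 or 2.5. Dropout is 20% in each arm. The true conditional HR is 0.26.

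**Early loss** (before any follow-up interview). Within arm k, the proportion free of onset among those retained is S_k = E_k[exp(−Λ·b_k·e^(γx))], with b = 1 in control and 0.26 in the active arm. Λ is set so that control incidence is 8.8% without dropout. E_k is taken over those who stay. Where dropout is linked to severity, its probability is 1/(1 + exp(−(a + x))), that is, log-odds 1 per SD, with a chosen to give 20% overall. Where it is not linked, it is a constant 20%. The condition-only HR is approximately ln S_active / ln S_control. Numerical integration gives:

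| Onset HR per SD | No dropout | Same link in both arms | Link in active arm only | Link in control only |
|---|---|---|---|---|
| 1.5 | 0.262 | 0.261 | 0.242 | 0.283 |
| 2 | 0.265 | 0.264 | 0.229 | 0.306 |
| 2.5 | 0.271 | 0.267 | 0.220 | 0.328 |

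The gap between 0.26 and the no-dropout column is non-collapsibility, not bias. In simulations of early active-arm loss at 2 to 2.5 per SD, with 15 to 20% dropout, the severity-adjusted HR was 0.255 to 0.265.

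**Loss spread over two years.** Simulation of 4 million participants per scenario, onset HR 1.5 to 3 per SD, dropout HR 2 to 3 per SD:

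- same link in both arms: unadjusted 0.260 to 0.273, against 0.261 to 0.277 with no dropout;
- active arm only: 0.245 to 0.254;
- control only: 0.271 to 0.303;
- adjusted HR in all the arm-differential patterns: 0.257 to 0.262.

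**Size against noise.** |ln(0.22/0.26)| = 0.17 and ln(0.33/0.26) = 0.24. These are about a quarter to just over a third of the standard error of 0.65.

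**Absolute measures.** An HR of 0.26 implies active-arm incidence 1 − (1 − 0.088)^0.26 = 2.4%, hence NNT = 1/(0.088 − 0.024) ≈ 16. Severity-related dropout that acts alike in both arms lowers estimated control incidence to between 7.6% and 8.5% and raises the NNT to 16 to 18, although the HR barely moves.

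**Cost of one covariate.** In 3,000 simulated trials of 147 per arm, Wald power unadjusted versus adjusted was 63.6% vs 64.6% (HR 2 per SD), 63.4% vs 65.9% (2.5) and 64.6% vs 67.3% (3). A further simulation put the gain at up to about 6 points. Null rejection with adjustment was 3.7 to 3.9% (Wald) and 4.4 to 5.0% (likelihood ratio).

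**The case against.** **Silence is not exclusion.** The article never says that covariates are barred from the Cox model, and a covariate list often sits in an analysis plan that is not shown. This stands, so the point cannot be that the plan rejects adjustment. What the article does print is a reason for ignoring missing onset data, and that reason is incomplete.

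**The continuous models are not a true parallel.** They adjust for the pretest value of the same outcome, and first onset has no such value. This also stands. The contrast that matters is in the missing-data assumption, not in the form of the adjustment.

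**A reader might infer that severity-related dropout as such biases the HR.** The documents do not support that. Dropout that acts alike in all arms leaves the HR nearly unchanged, and the article gives no dropout rate, no link with severity and no difference by arm. The one related figure, adherence typically above 80% and similar for groups and videos in an earlier trial, concerns sessions and viewing. It neither shows nor rules out differential loss to follow-up. Nor does anything fix the direction: loss linked to severity in the control arm alone makes the HR conservative.

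**The larger shifts assume early loss.** This is correct. Anyone lost before the 1-year interview contributes no onset information, so early loss is relevant, but nothing says that all loss occurs then.

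**Adjustment changes the estimand.** The adjusted HR is conditional, whereas the planning rates and the NNT are marginal. Reporting both HRs answers this.

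**Conclusion.** The point holds as a modest improvement. The stated rationale for not handling missing onset data is incomplete, and a model with condition only needs dropout to be unrelated to onset within each arm. If the severity–dropout link differs by arm, a true 0.26 could appear as about 0.22 to 0.33 with early loss, or about 0.25 with active-arm loss spread over two years. These figures rest on an assumed 20% dropout and the assumed prognostic strengths above. The shift is well inside sampling error and would not by itself overturn the trial's conclusion. It is still worth removing, because the covariate is already collected before randomization and including it did not inflate type I error in the control comparisons.

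Two limits remain. A baseline covariate does nothing about dropout driven by worsening after baseline, and it does not correct a crude NNT.

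**What to change.** 1. Pre-specify baseline EDE-Q global score as one continuous covariate in the Cox comparisons of each *Body Project* arm with control. The article lists four subscales, so state how the global score is formed.
2. Report the unadjusted HR beside the adjusted one, and label the adjusted HR as conditional.
3. Replace the right-censoring rationale with the assumption actually made: censoring is independent of onset given condition and baseline severity. Report dropout by arm and baseline severity so that readers can judge it.
4. For peer versus clinician, with about 6 expected onsets, treat the adjusted estimate with caution. The power and type I error checks above relate to the comparison with about 16 onsets.
5. Consider a sensitivity analysis such as inverse-probability-of-censoring weighting, and do not present a crude NNT as if the covariate had corrected it.

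The cost is a few lines in the analysis plan and one extra model parameter. No new data are needed.

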
### Power calculation

Sample size calculation was made for incidence of EDs assessed over a 2-year follow up via diagnostic interviews as the primary endpoint. Incidence rates were obtained from the previous Swedish virtual *Body Project* RCT [16]. Based on this trial we postulated a difference in incidence of EDs of 8.8% and 2% between groups, and a hazard ratio of 0.26 during 2 years of follow-up. Then, with a significance level of 5% and a power of 90% the estimated number of patients needed was 147 in each arm, the total number needed was 441.

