The *Body Project*, a selective 4-hour group-based program designed specifically for young women at risk for EDs, has the strongest evidence of effectiveness in reducing ED risk factors (such as thin-ideal internalization and body dissatisfaction) and ED symptoms [9], as well as preventing future ED onset among young women [10]. The evidence base for the *Body Project* is strong and based on over 20 controlled trials including assessment-only controls [11–13] and alternative credible interventions [14, 15]. Participants who complete the *Body Project* have shown a 60% reduction in future onset of EDs relative to assessment-only control participants [14] and a 54–58% reduction in future onset of EDs relative to alternative interventions [15]. The *Body Project* was originally designed as a face-to-face intervention, limiting availability to those who could attend in person. To reduce barriers to access, Ghaderi et al. [16] examined the effectiveness of virtually delivered *Body Project* groups (1 h a week over four consecutive weeks), through Google Hangouts, among young women (N = 443) aged 15–20 years. The participants were randomized to three conditions; (i) virtually delivered *Body Project* groups; (ii) expressive writing; and (iii) wait-list control group. Groups were facilitated by psychology undergraduates. The wait-list group received the *Body Project* after the 6-month follow-up. At two-year follow-up, *Body Project* participants compared to control participants showed a 77% lower incidence of ED onset and significantly greater reductions in ED symptoms and risk factors. This suggests that virtual *Body Project* groups may be an effective prevention strategy for individuals at risk of EDs, with an increased outreach. Moreover, in-person *Body Project* groups led by peer group facilitators produced a 58% greater reduction in future onset of EDs over 4-year follow-up when implemented by peer educators versus clinicians [15], theoretically because peers are perceived as more similar to the participants and thus have greater credibility. Whether these findings extend to virtual *Body Project* groups is unclear. Peer-led groups demand fewer resources to carry out than clinician-led groups, which may facilitate broader implementation.

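### The 90% power claimed for 147 per arm is about 77% for the planned two-sided comparison of one *Body Project* arm with control

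*Protocol article*

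**What the plan says.** The Power calculation section of the protocol article fixes the endpoint: "Sample size calculation was made for incidence of EDs assessed over a 2-year follow up via diagnostic interviews as the primary endpoint". Its planning values come from the earlier Swedish virtual trial: "we postulated a difference in incidence of EDs of 8.8% and 2% between groups, and a hazard ratio of 0.26 during 2 years". From these it concludes that "with a significance level of 5% and a power of 90% the estimated number of patients needed was 147 in each arm", and that "the total number needed was 441". It names no formula or test, does not say whether the 5% is one-sided or two-sided, and does not say which groups the two incidences belong to.

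The Statistical analyses section supplies the comparison. Onset is analysed with Cox proportional hazards models, each condition against each other condition, every test at 0.05. The Design section has three arms, so 147 in each means equal allocation. In the Background section the same Swedish trial is described as one in which participants "showed a 77% lower incidence of ED onset" at two years.

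**The concern.** The section prints every quantity needed to check it, and they do not fit together. With 8.8% and 2%, 294 participants in a two-arm contrast yield only about 16 onsets, and the usual formulas ask for more than that at 90% power. The hazard ratio also looks out of line with the two incidences.

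This is the primary endpoint. If the type II error for an arm-against-control comparison is nearer 23% than 10%, a non-significant result would be read as stronger evidence of no effect than the design can provide.

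**Working it through.** **Inputs (Power calculation section).** Risks 0.088 and 0.02; hazard ratio 0.26; significance 5%; power 90%; 147 per arm. Assumptions: two-sided test, no loss, everyone at risk of onset, one *Body Project* arm against control.

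**1. Attempt to reproduce 147 (two-sided, 90%).**
- Schoenfeld: events = 4(1.960 + 1.2816)² / (ln HR)². At 0.26 this is 23.16. The mean risk is (0.088 + 0.02)/2 = 0.054, so the total is 23.16/0.054 = 429, or 215 per arm.
- Schoenfeld at 0.219 (see step 3): 18.26 events, total 338, or 170 per arm.
- Two proportions: (1.960 × 0.3196 + 1.2816 × 0.3160)² / 0.068² = 230.1, or 231 per arm.
- Other methods: arcsine 208, Lachin-Foulkes 236, Freedman 238 (HR 0.219) or 283 (HR 0.26).

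None gives 147.

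**2. Power at 147 against 147.** Expected events are 294 × 0.054 = 15.88.

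| Method | Two-sided 5% | One-sided 5% |
|---|---|---|
| Schoenfeld, HR 0.26: √15.88 × 1.347/2 = 2.684, minus 1.960 or 1.645 | 76.5% | 85.1% |
| Schoenfeld, HR 0.219: √15.88 × 1.517/2 = 3.023, minus 1.960 or 1.645 | 85.6% | 91.6% |
| Exact enumeration of chi-square, 8.8% v 2.0% | 76.7% | 85.6% |
| Simulated log-rank, 8.8% v 2.0% (20,000 runs) | 77.4% | 86.0% |
| Two-proportion normal formula | 73.5% | 82.8% |

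Only one cell exceeds 90%: one-sided Schoenfeld at a hazard ratio that the section does not print. Simulation of the same one-sided situation gives 86%.

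**3. Hazard ratio against incidences.** Under proportional hazards, HR = ln(1 − 0.02)/ln(1 − 0.088) = 0.0202/0.0921 = 0.219. Conversely, 0.26 with 8.8% in controls implies 1 − 0.912^0.26 = 2.37%. A printed 2% covers about 1.5% to 2.49%, which corresponds to hazard ratios of 0.164 to 0.274, so 0.26 lies inside the rounding range.

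**4. Power if 2% stands for 2.37%.** Pairwise two-sided power at 147 per arm is 69.6% by exact chi-square and 70.1% by simulated log-rank. Schoenfeld, with 147 × (0.088 + 0.0237) = 16.4 events, gives 78%.

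**5. Pooled contrast, 294 against 147, two-sided.** Exact chi-square gives 90.0% at 8.8% v 2.0% and 85.1% at 8.8% v 2.37%; simulated log-rank gives 90.1% and 84.9%.

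**The case against.** Sidedness is not stated, and the hypotheses are directional. A one-sided 5% Schoenfeld calculation with a hazard ratio of 0.23, which matches the 77% reduction in the Background section, needs 15.86 events, and 15.86/0.108 = 146.8, which is 147 per arm. So a standard formula can return the printed number. This stands as a possible origin but does not rescue the text. The section prints 0.26, for which the one-sided calculation needs 175 per arm and gives about 85% at 147. A one-sided basis would also have to be declared.

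The contrast is not stated either. One working title in the Publication plan sets the virtual *Body Project* against control, which could mean both arms pooled, and pooled power is about 90% at 8.8% against 2.0%. That also stands, but the sizing is given per arm and the planned Cox tests are pairwise.

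Three stronger readings are tempting, and the article does not support them:
- *The hazard ratio is an error.* A reader might infer this from 0.22 against 0.26. It fits a rounded 2.4%, and it might be a Cox estimate from the source trial, which need not equal the ratio derived from two cumulative incidences.
- *Ignoring loss to follow-up is a mistake.* A condensed article may leave an allowance for loss to the full protocol.
- *The effect should have been the 54–58% "reduction in future onset of EDs relative to alternative interventions".* The section chose the trial closest in delivery mode. Preferring another source is a planning judgement.

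**Conclusion.** The stated power is wrong as written for the comparisons that the article plans. For one *Body Project* arm against control at two-sided 5%, 147 per arm gives about 77% at 8.8% against 2.0%. The type II error is then about 23%, more than twice the stated 10%. On the most favourable two-sided formula (Schoenfeld at 0.22) power is 86% and the type II error 14%. If the 2% is really 2.4%, which is what makes 0.26 consistent, power is about 70% by chi-square or log-rank. Two-sided 90% at the printed values needs roughly 170 to 230 per arm, depending on the method.

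These figures assume no loss, no multiplicity adjustment and all participants at risk of onset. The Participants section also admits people who already have an eating disorder diagnosis; if they cannot count as new onsets, power would be lower. No effect is postulated for peer-led against clinician-led groups, so none of these figures applies to that contrast.

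The finding concerns the stated power. It does not show that the trial must be enlarged.

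**What to change.** Rewrite the Power calculation paragraph:

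- Give the incidence to one decimal place with the hazard ratio that matches it: 8.8% and 2.0% with 0.22, or 8.8% and 2.4% with 0.26.
- Name the test or formula, its sidedness and the contrast being powered.
- Restate two-sided pairwise power at 147 per arm, before any loss, as about 77% for the first pair or about 70% for the second (chi-square or log-rank).
- Say that, two-sided, a pooled *Body Project* (294) against control (147) comparison reaches about 90% or about 85% respectively. If that is the comparison the 90% was meant for, add it to the Statistical analyses section.
- Optionally, add power under an assumed loss to follow-up and at a 54–58% reduction, labelled as sensitivity scenarios.

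The cost is one paragraph, plus one sentence in the analysis section if the pooled test is adopted. No participants are added. The price is a less favourable stated power for the pairwise tests.

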### Participants

A total of 441 young women will be included in the study. Inclusion criteria are being female, age between 16 and 25 years, and at least some level of self-reported body dissatisfaction verbally confirmed by the participant in the screening call, following procedures used in previous trials [14, 15, 31]. Participants diagnosed with an ED will also be included. These individuals have shown to display larger reductions in ED symptoms than participants without EDs in response to the *Body Project d* = 0.71 vs. 0.17) [32]. Exclusion criteria include being hospitalized or currently in treatment for an ED.

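### The 441 enrolled equals the 441 said to be needed for 90% power, so nothing is allowed for loss to follow-up; the stated inputs give about 77% at full follow-up and less with any loss

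*Protocol article*

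**What the plan says.** The Power calculation section names onset of eating disorders over two years, found by diagnostic interview, as the primary endpoint. It takes "a difference in incidence of EDs of 8.8% and 2% between groups" from an earlier Swedish trial, together with "a hazard ratio of 0.26 during 2 years of follow-up". At a 5% significance level and 90% power it concludes that "the estimated number of patients needed was 147 in each arm, the total number needed was 441".

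The Participants section states: "A total of 441 young women will be included in the study". The abstract gives the same total.

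The Procedure section places diagnostic interviews at baseline, 1 year and 2 years only. The Statistical analyses section plans Cox models that "will test whether eating disorder onset over 2-year follow-up was significantly lower in each condition versus each other condition". On missing data for this endpoint it says: "Because hazard models accommodate right censoring, we will not impute missing incidence data".

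No section gives an expected dropout rate or says whether follow-up was taken as complete. The figure of over 80% under Control condition concerns adherence to sessions and videos, not retention.

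**The concern.** The number needed and the number enrolled are the same, so any woman who leaves reduces the information below what the calculation calls necessary. Censoring is a legitimate way to analyse such women, but it does not bring back the onsets that go unobserved. A woman who misses both follow-up interviews contributes nothing to the onset comparison. One lost after the 1-year interview contributes only her first year.

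The endpoint is rare: about 16 onsets are expected in one active arm plus control, so losing two or three matters. If the trial ends without a significant difference in onset, readers will judge that result against the printed 90%. If the real figure is nearer 70%, they will give a null result too much weight.

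**Working it through.** **Inputs.** From Power calculation: two-year incidences 8.8% and 2%, hazard ratio 0.26, 5% level, 90% power, 147 per arm. From Procedure: interviews at 12 and 24 months. From Statistical analyses: pairwise Cox comparisons, "we will use a p-value of 0.05 for all inferential tests", and censoring of missing onset data. Assumptions of this check: a two-sided test (sidedness is not stated), and two-year loss of 10%, 20% or 30%, unrelated to onset.

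**1. Does 147 per arm reproduce?** Schoenfeld's formula gives the required events as 4(1.960 + 1.282)² / (ln 0.26)² = 23.2, so 24. Expected onsets per pair of women, one in each arm, are 0.088 + 0.020 = 0.108. The number per arm is 24 / 0.108 = 222.2, so 223. Other standard methods, two-sided, give 231 (two proportions), 208 (arcsine) and 288 (Freedman). One-sided versions give 169 to 232. All exceed 147 before any dropout, so 441 cannot contain a hidden allowance for it. A figure near 147 or 441 appears only with inputs or readings that the text does not state: a one-sided test with hazard ratio 0.23, or 441 read as a two-arm total.

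**2. Power at 147 per arm with full follow-up.** Expected onsets are 147 × 0.108 = 15.9. Schoenfeld power is Φ(√15.876 × |ln 0.26| / 2 − 1.960) = Φ(0.724) = 76.5%. Two proportions give about 73.5% and Freedman about 65%. A log-rank simulation (200,000 trials, interviews at 12 and 24 months) gives 76.7%. The two rates imply a hazard ratio of ln 0.98 / ln 0.912 = 0.22. If 0.26 is held instead, simulated power is about 70%.

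**3. Adding loss.** In the same simulation, annual dropout is 1 − √(1 − D) for a two-year loss D, and women stay in the analysis up to their last interview. The last column scales the printed claim by the ratio of events: Φ(3.2415 × √(events / 15.87) − 1.96).

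| Assumed two-year loss | Expected onsets | Log-rank power | Power if 90% were right at zero loss |
|---|---|---|---|
| 0% | 15.9 | 77% | 90% |
| 10% | 14.7 | 73% | 88% |
| 20% | 13.5 | 70% | 85% |
| 30% | 12.2 | 65% | 81% |

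From the 77% start, a fall of 5 points is reached at about 14% loss, and the fall at 20% is about 7 points. From a 90% start, the 5-point fall comes at about 20%.

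**4. Timing of loss.** At 20% loss, power is about 67% if all loss comes before the 1-year interview, 70% if it is spread, and 72% if all comes after that interview.

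**5. Women with an eating disorder at baseline.** The Participants section admits them, and they cannot have a new onset. Purely as an illustration, take the 16% that the Background cites for adolescent girls. Then 147 × 0.84 = 123.5 women per arm are at risk. At 10% loss, expected onsets are about 12.3 and power is about 65%.

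**The case against.** The strongest reply is that this is a condensed article. An expected retention rate is something the full protocol or analysis plan would normally hold, and its absence here is no defect. Right-censoring is also standard and contradicts nothing in the sizing. Both statements are fair, and silence about retention would not carry the point alone. The point stands because the article prints a full derivation, and no attrition assumption held elsewhere could make its 90% true for 441 enrolled.

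A second reply concerns the borrowed rates. If 8.8% and 2% are crude proportions of all women randomised in the Swedish trial, that trial's losses are already in them, and thinning the events again counts attrition twice. If they are Kaplan-Meier estimates, the thinning is right. The article does not say which, so this stays open and could shrink the falls in step 3. It does not affect the 77% at full follow-up.

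Some stronger readings are not supported:

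- A reader might infer that dropout is the main reason why 90% fails. At 10% loss, about 13 of the 17 points between 90% and 73% come from 147 per arm not reproducing, and about 4 from dropout.
- A reader might infer that the article declares complete follow-up. It does not. What can be said is that it leaves no margin for loss.
- A reader might treat a fall of 4 to 12 points as what this trial will suffer. That range rests on the assumed 10% to 30% loss and the 77% start. From 90% it is about 2 to 9 points.
- A reader might conclude that the planned events cannot be reached. The article sets no event target, and event counts vary by chance.

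**Conclusion.** The point holds in this form. The article enrols exactly the number it calls necessary, makes no allowance for loss, and attaches 90% power to a sample that its own inputs do not support at that level. For one active-versus-control contrast, 147 per arm gives about 77% by log-rank at full follow-up, and about 73%, 70% and 65% at assumed losses of 10%, 20% and 30%.

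These figures rest on a two-sided 5% test, the 8.8% and 2% rates, loss that is even over time and unrelated to onset, and all 147 women per arm being at risk. They would be lower with hazard ratio 0.26 in place of the 0.22 implied by the rates, or once women with an eating disorder at baseline are removed. The falls due to dropout would be smaller if most loss follows the 1-year interview or if the borrowed rates already reflect attrition.

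**What to change.** In Power calculation, remove the claim that 441 enrolled meets the number needed for 90% power. In its place, give the power and expected number of onsets for 441 randomised, for one active-versus-control contrast, at an expected two-year interview retention that is stated and labelled as an assumption. Say whether the test is one- or two-sided, whether the borrowed incidences are crude or Kaplan-Meier, and how many of the 441 are expected to be free of an eating disorder at baseline. Only those women should count as at risk. The 73% and 70% above should not be copied in as they stand, because they treat every participant as at risk.

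The cost is a rewritten paragraph and a less favourable stated power. Enrolment, conduct and analysis do not change.
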